## Materials and methods

### Study design and principal aims

The BAPS is a clinic-based, multicenter, noninterventional trial conducted on a sample of urban Chinese adults. This study has been approved by the ethics committee of Peking University People’s Hospital and will adhere to the tenets of the Declaration of Helsinki. The protocol is prospectively registered at www.cilinicaltrials.gov (registration number NCT05563623). Institutional Review Board/Ethics Committee approval has been obtained.

The comprehensive study protocol is summarized in Table 1, providing an overview of the study design and key steps.

**Table 1 tab1:** Comprehensive study protocol for the Beijing angle closure progression study.

Step	Description	Details
Study design	Clinic-based multicenter noninterventional trial	Conducted on a sample of urban Chinese adults
Ethics approval	Approved by the Ethics Committee	Peking University People’s Hospital, follows the Declaration of Helsinki
Registration	Protocol registered	www.clinicaltrials.gov (NCT05563623)
Participant recruitment	Recruitment centers	8 participating centers
Inclusion criteria	Criteria for eligibility	6 or more clock hours of angle circumference with no PAS and normal IOP Aged 40–75 years Provide informed consent
Exclusion criteria	Criteria for exclusion	Evidence of PAC or PACG Previous intraocular surgery or laser treatment Severe health problems
Baseline examination	Comprehensive initial examination	Visual acuity IOP measurement Slit-lamp biomicroscopy Gonioscopy OCT UBM
Follow-up visits	Regular follow-up schedule	Every 12 months, including examinations for IOP, visual acuity, gonioscopy, UBM, OCT, and visual field testing
Study endpoints	Criteria for study endpoint	Acute PAC episode Elevated IOP (>21 mmHg) Presence of PAS Glaucomatous visual field defects
Data management	Handling and storing data	Non-image data in BAPS Database Image/original data stored securely Privacy of participants protected
Statistical analysis	Data analysis methods	SPSS 22.0 for analysis Significance level: 0.05 Independent *t*-test, Mann–Whitney U test, Pearson chi-square test, logistic regression analysis, Cox regression analysis

IOP, intraocular pressure; PAS, peripheral anterior synechiae; PAC, primary angle-closure; PACG, primary angle-closure glaucoma; OCT, optical coherence tomography; UBM, ultrasound biomicroscopy; BAPS, Beijing angle closure progression study.

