### Sample size estimation

Currently, many studies have reported the prevalence of PACS in the population, with rates ranging from 4.68% (95% Confidence Interval [CI]: 4.541–4.819%) to 10.4% (95% CI: 9.6–11.2%) (7–9, 18–21). However, few studies have investigated the incidence of PACS progressing to PAC or PACG (11, 12, 15, 22, 23). In a population-based prospective study conducted in India, 11 out of 50 PACS eyes (22%; 95% CI: 9.8–34.2%) developed PAC over 5 years (23). Another follow-up study in Denmark involving 75 PACS eyes reported a progression incidence of 16% (15). Given the similarity between our sample characteristics and those in the Indian study, we conservatively estimated the incidence of PACS progressing to PAC or PACG at 20%. To analyze the risk factors, we plan to collect a larger sample size than previous studies. Considering the number of candidate risk factors and the prevalence of PACS, we will use standard sample size calculation formulas for proportions, aiming for a desired level of statistical power of 80% and a significance level of 0.05. Based on these calculations, we estimate that 700 subjects are needed to achieve reliable results. Accounting for an anticipated attrition rate of up to 15%, we set the final sample size at 825 individuals, expecting to have complete follow-up data for 700 individuals at the end of the study.

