### Clinical data collection

All subjects will be screened through a preliminary survey to verify their eligibility for recruitment in this trial. A comprehensive baseline examination will be conducted for every enrolled subject. Patients will be monitored for 5 years. All examinations involving subjective judgment and manipulation, such as Goldmann applanation (GAT), UBM, and gonioscopy, will be performed by experienced examiners.

For the analysis, we will enroll only one eye per subject to avoid correlation issues between eyes of the same individual. The selection of which eye to include will be randomized to ensure that there is no selection bias.

Inclusion criteria are as follows: (1) Static gonioscopy identifying six or more clock hours of angle circumference in which the posterior (usually pigmented) trabecular meshwork is not visible in both eyes with no PAS, and normal IOP, optic nerve, and visual field; (2) Patients aged between 40 and 75 years; and (3) Patients capable of providing informed consent.

Exclusion criteria are as follows: (1) Any evidence of PAC, characterized by a narrow angle as defined above, but with PAS and/or IOP > 21 mmHg, or PACG, indicated by a visual field defect or glaucomatous optic neuropathy; (2) Previous intraocular surgery or laser treatment, including cataract surgery, laser trabeculoplasty, trabeculectomy, laser peripheral iridectomy, and laser iridoplasty; (3) Signs of prior acute attack, such as glaucomatous fleck, keratic precipitates, or iris atrophy; (4) Anterior segment structural abnormalities, such as iris or ciliary body tumor; (5) Severe health problems that preclude follow-up, such as end-stage heart disease, kidney disease, lung disease, or terminal cancer; (6) Severe eye diseases requiring treatment, such as cataract, macular disease, and retinal detachment; and (7) Patients who plan to move from the area within the next 5 years.

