### Study endpoint and termination of follow-up (censored data)

The study endpoint will be reached if the participant meets any of the following criteria: (1) An episode of acute PAC; (2) Any PAS; (3) IOP > 21 mmHg; (4) Any patchy TM pigmentation; and (5) Glaucomatous visual field defect, RNFL defects, or glaucomatous abnormality of optic nerve. Participants meeting at least one of the five criteria will be classified in the progression group. For patients experiencing an acute angle-closure attack, the time of progression will be recorded accurately. If chronic progression (PAS or glaucomatous abnormality of optic nerve) is detected during routine follow-up, the progression time will be recorded based on the follow-up time.

The following conditions will be considered reasons for termination of follow-up and will be defined as censored data: (1) Inability to continue follow-up for various reasons, such as severe systemic diseases or relocation; (2) Development of new severe ocular diseases requiring treatment, such as vision-threatened cataract, retinal detachment, or age-related macular degeneration; (3) Missing 3 out of 6 monthly follow-up visits; and (4) Requesting withdrawal of informed consent.

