## Discussion

The BAPS is a multicenter, randomized, observational trial designed to explore the 5-year incidence of PACS progressing to PAC or PACG and to determine the risk factors for disease progression. The study hypothesizes that a subset of PACS patients, despite having similar initial presentations, might be predisposed to a faster disease progression, while others may remain relatively stable over time. By thoroughly analyzing and understanding the variables contributing to this divergence in disease course, we aim to identify high-risk PACS individuals who are more likely to developing PAC or PACG. This could enable better clinical decisions regarding whether to opt for prophylactic treatment or continued observation for these high-risk patients.

Although awareness of glaucoma screening is gradually increasing, the prevalence of PAC and PACG is as high as 1% in China (5, 6). Since the mid-1970s, LPI has been considered the first-line therapy for PAC and PACG (29). However, several randomized trials of screening and prophylactic LPI in patients with PACS conducted in Asia have reported no benefit in preventing vision loss due to glaucoma or in slowing the progression of the disease (17, 30). An Indian study demonstrated that LPI accelerates the progression of cataracts over a 6-years follow-up (31). Additionally, LPI may cause structural zonular damage and occult lens subluxation (32). Despite eye care providers being aware of these potential complications, a large number of LPI are still performed due to the fear of PACS rapidly evolving into PAC or PACG (33, 34). Therefore, identifying patients with high-risk PACS is critical both for reducing complications from LPI and for mitigating damage to visual function from PAC and PACG.

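### The endpoint and censoring lists leave out LPI, iridoplasty and IOP-lowering treatment given during follow-up, so a treated eye that keeps attending counts as untreated and non-progressing

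*Protocol article*

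**What the plan says.** The article describes an untreated cohort: "The BAPS is a clinic-based, multicenter, noninterventional trial conducted on a sample of urban Chinese adults". Its aim is the 5-year incidence of progression and the risk factors for it.

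- **Entry (Clinical data collection; Eligibility questions).** The exclusions include "Previous intraocular surgery or laser treatment, including cataract surgery", with laser iridectomy and iridoplasty also named. A screening question removes anyone already treated for glaucoma.
- **Endpoint (Study endpoint and termination of follow-up).** There are five criteria: acute PAC, PAS, IOP above 21 mmHg, patchy pigmentation of the trabecular meshwork, and glaucomatous field, nerve-fibre-layer or disc change. None is a treatment.
- **Censoring (same section).** There are four reasons: inability to continue, "Development of new severe ocular diseases requiring treatment, such as vision-threatened cataract, retinal detachment, or age-related macular degeneration", missed visits, and withdrawal of consent.
- **Analysis (Statistical analysis plan).** A progression rate, then logistic and Cox regression for risk factors.
- **Discussion.** LPI is common in practice: "a large number of LPI are still performed due to the fear of PACS rapidly evolving into PAC or PACG". The same paragraph reports randomized trials in which prophylactic LPI gave no benefit. The Discussion then sets aside an earlier narrow-angle cohort as evidence on natural history, partly because its patients received IOP-lowering drugs.

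**The concern.** Treatment disqualifies an eye on the day of entry but has no stated consequence the day after. None of the four censoring reasons fits an eye lasered for PACS itself: the patient can continue, has no new disease, attends visits and has not withdrawn. Such an eye therefore stays in the risk set and, if no endpoint occurs, joins the non-progression group.

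Two results are exposed. The 5-year incidence would describe a mixture of treated and untreated eyes. If treatment works and goes more often to eyes that look at risk, the features that prompt it would appear less predictive than they are. IOP-lowering drugs add a direct route, because IOP above 21 mmHg is itself an endpoint criterion that a drug could suppress. If treatment dates are not collected, none of this can be repaired at analysis.

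**Working it through.** **The plan's own figures.** The article "conservatively estimated the incidence of PACS progressing to PAC or PACG at 20" per cent. It then states: "we estimate that 700 subjects are needed to achieve reliable results". Inflating for 15% attrition gives 700 / (1 − 0.15) = 823.5, or 824, which agrees with the stated 825. At 20%, 700 × 0.20 = 140 events are expected. The 95% half-width is 1.96 × √(0.2 × 0.8 / 700) = 0.030, about 3 points. None of these figures is disputed; they set the scale.

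**What the document does not give.** Treatment uptake, the relation of uptake to risk, and the hazard after treatment. All are assumed below.

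**Check A, two equal groups with true HR 2 and overall 5-year risk 20%.** With x the low-risk 5-year survival, (1 − x) + (1 − x²) = 0.40 gives x = 0.860. The group risks are 14.0% and 26.0%, and the low-risk 5-year cumulative hazard is 0.151. Let a fraction u be treated at times spread evenly over 5 years, and let θ multiply the hazard afterwards. About u/2 of the person-time is then post-treatment, so the group hazard is multiplied by roughly 1 − (u/2)(1 − θ).

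- u = 5% low and 20% high, θ = 0.5: multipliers 0.9875 and 0.95. Apparent HR = 2 × 0.95 / 0.9875 = 1.92; incidence about 19.4%.
- u = 5% low and 30% high, θ = 0.2: multipliers 0.98 and 0.88. Apparent HR = 2 × 0.88 / 0.98 = 1.80; incidence about 18.5%.

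Simulation with 2 million eyes per group, treatment ignored:

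| Uptake low / high | θ | Incidence | HR |
|---|---|---|---|
| 5% / 20% | 0.5 | 19.3% | 1.92 |
| 5% / 20% | 0.2 | 18.9% | 1.87 |
| 5% / 30% | 0.5 | 19.0% | 1.86 |
| 5% / 30% | 0.2 | 18.3% | 1.78 |

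Censoring at treatment returns an HR of 2.00.

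**Check B, continuous marker, 400,000 eyes.** True incidence is 20%, true HR per SD is 1.5 or 2.0, and the treatment hazard doubles per SD of the same marker. Ranges in the first two columns cover θ of 0.3 to 0.5; the incidence columns cover both true HRs.

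| Uptake | Incidence, ignored | HR 2.0 reads, ignored | Kaplan–Meier incidence, censored |
|---|---|---|---|
| 5% | 19.6–19.7% | 1.96–1.98 | 19.8% |
| 10% | 19.1–19.4% | 1.93–1.95 | 19.6–19.7% |
| 20% | 18.2–18.8% | 1.86–1.91 | 19.1–19.3% |

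At 20% uptake a true HR of 1.5 reads 1.42 to 1.45. With θ = 1 (no treatment effect) incidence stays at 20% and the HR at 2.0, at every uptake. When eyes are censored at treatment and the marker is in the Cox model, the HR is 1.50–1.51 or 2.00. The unadjusted Kaplan–Meier incidence stays slightly low because that censoring is informative. A binary analysis of the censored data reads 17.3–19.4% if censored eyes count as non-progressors and 20.2–21.2% if they are dropped.

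**Against sampling error.** The largest incidence shift, 20 − 18.2 = 1.8 points, is below the 3-point half-width. The largest log-HR shift, ln(2 / 1.78) = 0.117, is below one standard error, √(4 / 140) = 0.169 for equal groups.

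**The case against.** The strongest reply is that the document itself reports little or no effect of LPI: the Introduction calls the benefit of prophylactic LPI in PACS limited, and the Discussion cites trials showing no slowing of progression. If that holds for these eyes, leaving LPI out of the lists does no harm, as the θ = 1 runs show. This stands, and it is why the size cannot be stated. It does not close the gap. The article's rationale is to find patients in whom prophylactic treatment may be worthwhile, which leaves an effect in some of them open. The cited trials also concern LPI, not IOP-lowering drugs.

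A second reply is that treatment started because of IOP above 21 mmHg follows the endpoint and cannot mask it. That is right for those eyes, but not for drugs started before such a reading.

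A third is that a fuller protocol or data form may already record treatment. It may. The two lists are nevertheless given in the article, under a heading that names censored data, and as written they do not deal with it.

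Two stronger readings are tempting and not supported.

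- A reader might infer that the results are biased because the highest-risk eyes are treated. The document gives no uptake in the eight centers and does not say that the narrowest angles are treated more. The Discussion speaks of providers and PACS in general.
- A reader might infer that censoring at cataract is also an error, because lens surgery competes with progression. A Cox model that censors at cataract is already a cause-specific hazard model, and age and the lens measures are collected as possible covariates. The article names no Kaplan–Meier estimate. If lens surgery is independent of progression, one minus Kaplan–Meier returns the untreated 20%. The cumulative incidence of 18–19% (competing surgery in 10–20%) answers a different question.

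**Conclusion.** The gap is real and lies in rules the article states. Treatment of the study eye before an endpoint is in neither list, against the document's own entry exclusions and its own standard for natural-history evidence. The consequence is possible dilution of unknown size. It is nil without a treatment effect. Under assumed uptake of 5–30% and a post-treatment hazard multiplied by 0.2–0.5, it is up to about 2 points on 20%, and an HR of 2.0 reads about 1.8 to 1.9. Higher uptake or stronger selection would give more. The shift is smaller than sampling error at the planned size, but it is systematic, so a larger sample would not remove it. The correction is cheap and worth making while treatment dates can still be recorded. The point does not extend to cataract censoring.

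**What to change.** 1. Record the date, eye and type of any LPI, iridoplasty or IOP-lowering treatment given before an endpoint, if the data forms do not already do so.
2. Add such treatment of the study eye to the termination list as a reason that ends untreated follow-up. Censor there in the Cox model, with the baseline angle and lens measures as covariates.
3. Report a sensitivity analysis that keeps the follow-up after treatment, so that readers see how far the handling matters.
4. State how treated eyes enter the progression proportion and the logistic regression, since neither can use censored time.

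The cost is a few data fields and a sentence or two of text. The downside is the loss of post-treatment person-time and possible informative censoring, which the covariates reduce but may not remove. Competing-risk and inverse-probability-of-censoring-weighted analyses are optional. Nothing here implies a rule on when an eye should be treated.

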### Statistical analysis plan

All parameters measured in UBM will be calculated by averaging the corresponding measurements from both horizontal and vertical images. The normality of the data will be evaluated by using the Shapiro–Wilk test. Means and standard deviations will be calculated for all continuous variables. Baseline characteristics will be compared between progression group and non-progression group using the independent *t*-test or Mann–Whitney U test for continuous variables and the Pearson chi-square test for categorical variables.

The primary outcome is the progression rate, in other words, the rate of acute PAC (IOP > 21 mmHg) and the proportion of eyes developing PAS. We will evaluate the risk factors for PACS progression to PAC or PACG using univariable and multivariable logistic regression analysis, as well as Cox regression analysis. All statistical analyses will be performed using the software SPSS 22.0 (SPSS, Inc., Chicago, IL) with a significance level set at 0.05.

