**Methods/design:**

The BAPS is a clinic-based, multicenter, noninterventional trial conducted on a sample of urban Chinese adults. Consecutive eligible patients who meet PACS diagnostic criteria will be recruited from eight participating centers, with the trial commencing on August 4, 2022. The target sample size is set at 825 subjects, with follow up planned for a minimum period of 5 years. Baseline examination will include presenting visual acuity, best corrected visual acuity, intraocular pressure (IOP), undilated slit-lamp biomicroscopy, stereoscopic evaluation of the optic disc, visual field test, optical coherence tomography evaluation of retinal nerve fiber layer, ultrasound biomicroscopy and IOLMaster. Questionnaires will also be used to collect detailed personal history. Patients are scheduled to visit the glaucoma clinic every 12 months and may visit the emergency room in case of acute attack of angle closure. Study endpoints include acute PAC episodes, elevated IOP, peripheral anterior synechiae, glaucomatous visual field defect, or glaucomatous abnormality of optic nerve.

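### The primary outcome in the analysis plan counts fewer kinds of event than the five-criterion endpoint that forms the progression group, so the text yields two different 5-year incidences

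*Protocol article*

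**What the plan says.** The principal aim (Study design and principal aims) is the 5-year incidence of progression from PACS to PAC or PACG. The 20% planning rate in Sample size estimation is given for that same event.

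The section on study endpoint and termination of follow-up gives five criteria. The first four are "1) An episode of acute PAC; (2) Any PAS; (3) IOP > 21 mmHg; (4) Any patchy TM pigmentation" and the last is "5) Glaucomatous visual field defect, RNFL defects, or glaucomatous abnormality of optic nerve". One is enough: "Participants meeting at least one of the five criteria will be classified in the progression group".

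The Statistical analysis plan section treats the primary outcome as a restatement of progression: "The primary outcome is the progression rate, in other words, the rate of acute PAC". In full, the restatement is "the rate of acute PAC (IOP > 21 mmHg) and the proportion of eyes developing PAS". The same section then uses the grouping from the endpoint section: "Baseline characteristics will be compared between progression group and non-progression group". It words the target of the logistic and Cox models as progression to PAC or PACG.

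Two shorter lists appear elsewhere. Table 1 has four items and ends "Presence of PAS Glaucomatous visual field defects". The abstract says "Study endpoints include acute PAC episodes, elevated IOP, peripheral anterior synechiae, glaucomatous visual field defect, or glaucomatous abnormality of optic nerve".

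**The concern.** The analysis plan offers its short list as equivalent to progression, but the two lists are not equivalent. The short one leaves out patchy TM pigmentation and all glaucomatous damage. It also merges acute PAC with IOP > 21 mmHg, which the endpoint section keeps apart as criteria (1) and (3). Read literally, an eye whose only change is raised IOP without an acute attack is not a primary event, although the protocol elsewhere counts it as PAC.

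The mismatch runs the other way too. Patchy TM pigmentation alone makes a participant a progressor under the endpoint section, yet it is in neither the PAC nor the PACG definition, and the aim is PAC or PACG.

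At stake is the main descriptive result of the study. The reported incidence need not equal the share of participants in the progression group analysed beside it. While both definitions stand, the one used for the headline rate could be chosen after the results are known.

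**Working it through.** **Step 1: set the definitions side by side.** The last column combines the Introduction and exclusion criterion (1) in Clinical data collection.

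| Component | Endpoint section | Primary outcome, analysis plan | PAC/PACG as defined in the protocol |
|---|---|---|---|
| Acute PAC episode | yes (1) | yes | not named in the PAC definition |
| PAS | yes (2) | yes | PAC |
| Raised IOP, no acute attack | yes (3) | no if the bracket qualifies acute PAC; yes if it stands for raised IOP | PAC |
| Patchy TM pigmentation | yes (4) | no | not named |
| Glaucomatous field or optic-nerve damage | yes (5) | no | PACG; the Introduction asks for PAC features as well, the exclusion criterion does not say so |
| RNFL defect | yes (5) | no | not named |

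The two outcome columns give the same rate only if no participant progresses solely through a row in which they differ.

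**Step 2: the plan's own figures.** Inputs from Sample size estimation: 700 evaluable subjects, up to 15% attrition, 825 recruited, 20% incidence.

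- Recruitment: 700 / (1 − 0.15) = 823.5, rounded up to 824. The stated 825 agrees closely.
- Events at 20%: 0.20 × 700 = 140.
- 95% half-width at 20%: 1.96 × √(0.20 × 0.80 / 700) = 0.0296, or 2.96 percentage points.

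**Step 3: illustrate the gap.** The protocol gives no component rates, so the shares below are assumptions. It also does not say which list the 20% belongs to, so both directions are shown.

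*(a) 20% is the five-criterion rate.* A fraction f of progressors qualifies only through criteria that the analysis plan omits. Narrower rate = 20% × (1 − f); events = 700 × that rate.

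| f | Narrower rate | Events (against 140) |
|---|---|---|
| 10% | 18% | 126 |
| 25% | 15% | 105 |
| 40% | 12% | 84 |

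The shift exceeds the 2.96-point half-width once f passes 2.96 / 20 = 14.8%, about 15%.

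*(b) 20% is the narrower rate.* The extra criteria add a percentage points. Five-criterion rate = 20% + a.

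| a | Five-criterion rate | Events (against 140) |
|---|---|---|
| 2 | 22% | 154 |
| 5 | 25% | 175 |
| 10 | 30% | 210 |

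**The case against.** The strongest reply is that the clinical gap may be small. If the bracket in the analysis plan simply means raised IOP, then raised IOP plus PAS covers PAC as the protocol defines it. The Introduction describes PACG as those same features together with optic neuropathy or a field defect, so most PACG would be captured as well. On that reading the difference reduces to the word acute, TM pigmentation and damage-only cases. This is a fair limit on the size, and it means one cannot say that PACG is lost from the primary outcome. It does not remove the contradiction: the text does say acute PAC, the exclusion criterion words PACG more loosely than the Introduction, and TM pigmentation differs on any reading.

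A reader might infer that the progression group and the regression outcome are undefined too. The document does not support that. The endpoint section fixes the group, and the analysis plan names progression to PAC or PACG as the modelling target rather than its own short list. What remains open for the models is narrower: whether a progressor by TM pigmentation alone counts as having progressed to PAC or PACG.

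A reader might also count Table 1 and the abstract as third and fourth rival definitions. Table 1 is introduced as an overview, and the abstract says only what the endpoints include. They need aligning, but they are weak evidence of separate definitions.

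**Conclusion.** The point stands as a contradiction between two sections of the current text. Shortening for a journal does not explain it, because both definitions are printed and one is presented as a paraphrase of the other. It concerns the sentence that defines the headline rate and that rate's relation to the progression group.

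Its size is unknown. The figures of 12% to 18% in one direction and 22% to 30% in the other rest wholly on assumed shares, applied to 700 subjects and the planning rate. It would be tempting to say that the analysis plan understates a 20% rate. The document does not support this: it gives 20% for PAC or PACG, anchored on an Indian study in which 22% developed PAC and none PACG, and TM pigmentation belongs to neither category. The 20% may be nearer the narrower rate, with the five-criterion rate above it.

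Because this incidence is the principal aim, the definition should be settled before any outcome analysis.

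**What to change.** By dated amendment, before any outcome analysis:

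1. Reconcile the analysis plan with the endpoint section to one primary progression definition. Use it for the incidence, the group comparison, and the logistic and Cox models.
2. Replace the merged wording by listing acute PAC and IOP > 21 mmHg as separate components.
3. State whether patchy TM pigmentation and a stand-alone RNFL defect count towards progression to PAC or PACG. One workable option is to keep the five-criterion endpoint as primary and report the incidence without TM pigmentation as a sensitivity analysis.
4. Report each component separately, so that readers can see what drives the rate.
5. Align Table 1 and the abstract with the chosen definition.

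Recruitment began in August 2022, so if a criterion is removed, the amendment should record this as a change of endpoint and not as an editorial correction. The cost is the amendment and a few extra tabulations; no new data are needed.

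### The plan defines censored participants, but its primary outcome is a crude proportion and logistic regression stands beside Cox with neither primary

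*Protocol article*

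**What the plan says.** The principal aim, under Study design and principal aims, is the 5-year incidence of progression and its risk factors.

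- **Censoring.** The section Study endpoint and termination of follow-up states: "The following conditions will be considered reasons for termination of follow-up and will be defined as censored data". It lists inability to continue (for example severe systemic disease or relocation), new severe eye disease needing treatment (for example vision-threatening cataract), missed visits, and withdrawal of consent.
- **Event time.** Acute attacks carry their own date. For PAS or optic nerve change found at a routine visit, "the progression time will be recorded based on the follow-up time". Under Follow-up visits, the routine interval is 12 months.
- **Attrition.** Sample size estimation says: "Accounting for an anticipated attrition rate of up to 15%, we set the final sample size at 825 individuals". The authors thus count on 700 participants being fully followed.
- **Analysis.** The Statistical analysis plan section describes the primary outcome as a progression rate, explained as a rate of acute PAC and a proportion of eyes with PAS. It compares baseline characteristics between progressors and non-progressors by t-test, Mann-Whitney or chi-square. Risk factors are assessed "using univariable and multivariable logistic regression analysis, as well as Cox regression analysis". It names no time-to-event estimator for the incidence, ranks neither model, and does not say how a censored participant enters the proportion, the groups or the logistic model.

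**The concern.** A participant censored at year 2 without an event has an unknown 5-year status. A proportion, a two-group table and a logistic model all need a yes or no. Counting the participant as a non-progressor biases the incidence down, because some would have progressed by year 5. Dropping the participant biases it up, because people who progressed before they could be lost stay in while event-free people who leave go out. Recruiting more participants removes neither bias.

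For risk factors, the same coding distorts the odds ratio when attrition depends on the factor. The plan's own censoring reasons make that plausible. Cataract and severe systemic disease end follow-up, while age and lens measurements are natural candidate factors: the Introduction cites older age as a known risk factor, and lens grade, lens thickness and lens vault are measured at baseline.

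With two unranked models, there are also two answers to one principal question.

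**Working it through.** **Inputs from the article.** 5-year risk 20% ("we conservatively estimated the incidence of PACS progressing to PAC or PACG at 20" per cent); evaluable N 700; attrition 15%; enrolled N 825; visits every 12 months.

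**Assumptions of this check.** Constant hazards; dropout independent of progression; 15% is the chance of dropping out over 5 years; for associations, one binary factor with 50% prevalence and hazard ratio (HR) 2.0.

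**Step 1, the plan's own figure.** 700 / 0.85 = 823.5, so 824 against the stated 825. It reproduces and is not in dispute. The 700 cannot be re-derived, because no effect size or precision is given; this point does not depend on it.

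**Step 2, crude incidence with exact event dates.**
- Event hazard λ = -ln(0.80)/5 = 0.0446; dropout hazard μ = -ln(0.85)/5 = 0.0325.
- Observed events per person enrolled = λ/(λ+μ) × (1 - 0.80 × 0.85) = 0.5786 × 0.32 = 0.185.
- Event-free and followed to year 5 = 0.80 × 0.85 = 0.68.
- Censored counted as non-progressors: **18.5%**, a bias of -1.5 points.
- Censored dropped: 0.185 / (0.185 + 0.68) = **21.4%**, a bias of +1.4 points.

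**Step 3, the same with annual detection.** An event in year k is seen only if the person is still in follow-up at visit k. With s = 0.80^(1/5) and g = 0.85^(1/5), the observed share is (1 - s) × g × (1 - 0.68)/(1 - s × g) = 0.182.
- Counted as non-progressors: **18.2%** (-1.8 points).
- Dropped: 0.182 / (0.182 + 0.68) = **21.1%** (+1.1 points).
- Kaplan-Meier on the visit-dated times (simulation, N = 825, 300 replicates): **20.0%**.

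The 95% half-width at n = 700 is 1.96 × √(0.2 × 0.8/700) = 3.0 points, so each convention errs by about 0.4 to 0.6 of a half-width. At 5% attrition the annual-detection figures are 19.4% and 20.3%.

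**Step 4, associations.** With HR 2.0 and overall risk 20%, the two level-specific risks are 14.0% and 26.0%. The true 5-year odds ratio (OR) is (0.260/0.740) / (0.140/0.860) = 2.16. The Step 3 formula applied within each factor level, set beside the simulation, gives:

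| Attrition, factor absent / present | OR, censored = non-progressor: closed form (simulated) | OR, censored dropped: closed form (simulated) |
|---|---|---|
| 15% / 15% | 2.13 (2.15) | 2.17 (2.18) |
| 5% / 25% | 1.81 (1.81) | 2.40 (2.39) |
| 25% / 5% | 2.52 (2.58) | 1.96 (2.01) |

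Against 2.16, equal attrition leaves the OR within about 1.5%. With unequal attrition, the largest shifts in closed form are 1.81/2.16 = -16% and 2.52/2.16 = +16%; the simulation gives -16% and +19%. The upper figures differ through simulation error: Cox with exact times also ran high in that scenario (2.05 for a true 2.0). Visit-dated Cox stayed between 1.96 and 2.05 throughout.

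**Step 5, visit dating alone.** With every visit kept, Kaplan-Meier stays at 20.0% to 20.1%. With 10% to 30% of visits missed it is 20.1% to 20.7%. The HR moves by about 4% at most (2.0 to 1.93 or 2.06), even when the share of exactly dated acute events is 0% in one factor level and 50% in the other.

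**The case against.** **Cox is already planned.** It stands in the same sentence as logistic regression, and the endpoint section supplies event time and censoring rules. This is right: the plan does not lack a survival model. But Cox is not ranked above logistic regression, and listing it does not settle the incidence, whose stated form is a proportion.

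**This is a condensed article.** Which model is primary, and the exact estimator, may be fixed in a fuller document not at hand. That is fair for the ranking and for tie handling. The point rests on what the article does state: a proportion as primary outcome, and a logistic model, beside its own definition of censored data.

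**The group tests compare baseline characteristics only.** This is also fair. They need only be read as descriptive.

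Three stronger readings are tempting, and the documents do not support them.

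- *That the associations are biased.* This needs attrition to differ by factor. The 5%/25% split is an assumption, and the article gives no such figures. If dropout is related to progression itself, Cox and Kaplan-Meier suffer too.
- *That dating chronic events at the detecting visit biases the results.* Step 5 shows the effect is small.
- *That the error is as large as the confidence half-width.* The 2.9-point gap (21.4 - 18.5) lies between two mutually exclusive conventions. No single analysis incurs it.

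**Conclusion.** The point holds for the incidence. The primary outcome as stated has no valid place for censored participants, and either way of forcing them in misstates a true 20% by about 1 to 2 points at the plan's own attrition. That is about half the sampling half-width, but it is systematic and avoidable. The size rests on constant hazards, independent dropout and the article's 20% and 15%.

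For risk factors the conclusion is conditional. Logistic odds ratios are liable to bias, of the order of 16% to 19% in either direction under the assumed 5%/25% attrition split, and are close to correct if attrition is unrelated to the factor. Leaving logistic and Cox unranked is a weakness in its own right, because the choice could be made after seeing both.

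Visit dating is a secondary matter and does not by itself call for a different model.

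**What to change.** In the Statistical analysis plan section:

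1. Estimate 5-year incidence by Kaplan-Meier with a 95% CI, in place of the crude proportion. As a sensitivity analysis, use Aalen-Johansen with censoring for new severe eye disease treated as a competing event.
2. Name the already planned Cox model as the sole primary risk-factor analysis.
3. Keep logistic regression only as a labelled sensitivity analysis, with a written rule for participants censored before year 5.
4. State that the comparisons of progressors with non-progressors are descriptive.

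Optional: a discrete-time or interval-censored model for visit-detected events, as a further sensitivity analysis.

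The cost is a few sentences and modest programming. Visit and event times are already to be recorded, so no new data are needed and recruitment is unaffected.
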